### Sample collection

Two vaginal swabs, 2 cervical canal swabs, and 3 ml of peripheral blood will be collected on the day of the first clinic visit and the day of embryo transfer (ET). Vaginal swabs will be collected directly, while cervical canal swabs will be collected carefully through a vaginal dilator device to avoid contamination from contact with the vagina. Vaginal and cervical canal swabs will be immediately collected in a clean 2-ml DNA LoBind tube and immediately placed on ice and transferred to a − 80 °C freezer within 2 h, followed by DNA extraction. Peripheral venous blood will be collected in coagulation-enhancing disposable vacuum blood collection tubes. Blood will be centrifuged at 2000 rpm for 20 min at 4 °C (Eppendorf, Germany). Serum will be isolated and divided into 2 tubes and immediately frozen at − 80 °C until use.

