**Methods/design:**

This is a protocol for a multicenter, open-label, randomized controlled trial in China. Women diagnosed with PCOS who are undergoing IVF-FET treatment will be recruited. Allocation to the intervention/control arms at a ratio of 1:1 will be executed by an electronic randomization system. Participants in the intervention arm will receive the live *Lactobacillus* capsule vaginally for 10 consecutive days before embryo transfer, while those in the control arm will receive standard individualized care. The primary outcomes will be the clinical pregnancy rate, implantation rate, and live birth rate. 16S rRNA sequencing and liquid chromatography–mass spectrometry will be conducted to evaluate the LGT microbiome and systemic metabonomics before and after the intervention. A sample of 260 participants will provide 95% power to detect a 20% increase in the rate of clinical pregnancy (*α* = 0.025, one-tailed test, 15% dropout rate). A total of 300 participants will be recruited.

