### DNA extraction and quick screening by quantitative PCR

DNA extraction from a vaginal swab will be performed using the DNeasy Power Soil kit (12888, QIAGEN) according to the manufacturer’s instructions. The quantity and quality of DNA will be assessed by a NanoDrop 2000 (Thermo Fisher Scientific, USA). Quick screening for the relative abundance of *Lactobacillus* spp. in the vaginal microbiome will be performed by qPCR. The relative abundance of *Gardnerella vaginalis* and subtypes of *Lactobacillus* spp., including *Lactobacillus jensenii*, *Lactobacillus crispatus*, and *Lactobacillus ineris,* will also be evaluated. The sequences of primers used in qPCR are presented in Table 1. DNA will be amplified with TB Green® Premix Ex Taq™ (Tli RNaseH Plus) (RR420, Takara) using an ABI QuantStudio™ 7 Flex Real-Time PCR System. The abundance of *Lactobacillus* spp. will be calculated relative to that of total bacteria.

**Table 1 Tab1:** List of primers used for qPCR

Target	Forward	Reverse
Total bacteria	5′-AGAGTTTGATCCTGGCTCAG-3′	5′-GCTGCCTCCCGTAGGAGT-3′
*Lactobacillus* spp.	5′-AGAGTTTGAT/YM/TGGCTCAG-3′	5′-CACCGCTACACATGGAG-3′
*Lactobacillus jensenii*	5′-AAGTCGAGCGAGCTTGCCTATAGA-3′	5′-CTTCTTTCATGCGAAAGTAGC-3′
*Lactobacillus crispatus*	5′-AGCGAGCGGAACTAACAGATTTAC-3′	5′-AGCTGATCATGCGATCTGCTT-3′
*Lactobacillus ineris*	5′-CTCTGCCTTGAAGATCGGAGTGC-3′	5′-ACAGTTGATAGGCATCATCTG-3′
*Gardnerella vaginalis*	5′-TTACTGGTGTATCACTGTAAGG-3′	5′-CCGTCACAGGCTGAACAGT-3′

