### Intervention

For the intervention group, a live *Lactobacillus* capsule (> 1 × 10^6^ CFU/g, National Medicine Approval Number: S20030005, Inner Mongolia Shuangqi Pharmaceutical Co., Ltd., PRC) will be administered vaginally.

The live *Lactobacillus* capsule has been reported to be effective for bacterial vaginosis treatment with fewer adverse effects than antibiotics, and probiotic treatment for women with GDM has been reported to improve maternal and infant health outcomes [10, 17–19]. In the intervention group, 1 live *Lactobacillus* capsule per day will be applied transvaginally for 10 consecutive days starting on the initiation day of the FET cycle. Medical gloves will be included in the pill box, and the pills will be stored at 2–8 °C until use. The usage will be explained to the participants by the CRCs. A well-designed medication diary will be prepared to help remind patients and assist them in recording the process of medication administration (Table 2). Regular follow-up will be performed on day 5 and day 10 in both groups by phone call. Any adverse response will be recorded and reported at any time.

**Table 2 Tab2:** Medication diary

Medication diary			
Name:			
Date	Day Month Year	Day Month Year	Day Month Year
Live *Lactobacillus* capsule for vaginal use	□ Morning □ Evening ______pill	□ Morning □ Evening ______pill	□ Morning □ Evening ______pill
	Day Month Year	Day Month Year	Day Month Year
	□ Morning □ Evening ______pill	□ Morning □ Evening ______pill	□ Morning □ Evening ______pill
	Day Month Year	Day Month Year	Day Month Year
	□ Morning □ Evening ______pill	□ Morning □ Evening ______pill	□ Morning □ Evening ______pill
	Day Month Year		
	□ Morning □ Evening ______pill		

Please fill out the date and time after the daily use of 1 capsule

Please contact us if any symptoms of discomfort occur during medication use

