### Participant timeline

The time schedule of enrollment, intervention, follow-up and outcome assessments is shown in Table 3. After undergoing ovulation, egg retrieval, IVF, and advanced embryo freezing, PCOS patients will move on to the next step of endometrial preparation for FET. The duration of endometrial preparation will continue for approximately 14 days. At the 1st clinical visit on the first day of the current FET cycle, written informed consent, baseline information, 2 vaginal swabs, 2 cervical canal swabs, and 3 ml peripheral blood will be obtained at enrollment. After quick screening for the relative abundance of *Lactobacillus* spp. in vaginal flora, the participants will be informed of whether they have LGT dysbiosis and the results of randomization. At the 2nd visit after enrollment, in the control group, participants with LGT dysbiosis will confirm the next contact, while the intervention group will administer live *Lactobacillus* capsules vaginally and will be provided a medication diary. All participants will be followed up 5 times in the clinic or by phone call. The 3rd visit after 5 days of drug administration will mainly be about whether any adverse response occurs. At the 4th visit after 10 days of drug administration, the medication diary will be checked and reviewed, and any adverse response will be recorded and reported. At the 5th visit on the day of ET, 2 vaginal swabs, 2 cervical canal swabs, and 3 ml peripheral blood will be obtained from participants in both groups. At the 1st follow-up after 14 days of ET, human chorionic gonadotropin (HCG) and progesterone (P) levels will be determined as standard clinical procedures. If the HCG test is positive, the 2nd follow-up will occur approximately 5 weeks after ET, and clinical pregnancy will be confirmed by ultrasound and recorded in the CRIP system. At the 3rd follow-up, the fetal developmental situation and maternal obstetric complications at approximately 24-28 gestational weeks, if any, will be carefully recorded. The endpoint of follow-up is live birth, and maternal and neonatal information will be obtained.

**Table 3 Tab3:** Schedule

	1st visit on FET initial day	2nd visit after enrollment	3rd visit after 5 days	4th visit after 10 days	5th visit on ET	1st follow-up at 14 days after ET	2nd follow-up at 5 weeks after ET	3rd follow-up at mid-pregnancy	End of live birth

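### The single post-treatment swab, taken days after the last capsule and read as DNA share, describes the flora at transfer but cannot by itself show that dysbiosis was reversed

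*Protocol article*

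**What the plan says.** The Objectives section puts reversal of LGT dysbiosis first and better perinatal outcomes second.

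- **Sampling.** Under Sample collection, swabs and blood "will be collected on the day of the first clinic visit and the day of embryo transfer (ET"). The Participant timeline agrees: "At the 5th visit on the day of ET, 2 vaginal swabs, 2 cervical canal swabs, and 3 ml peripheral blood will be obtained". Table 3 marks swabs at these two visits only.
- **Treatment.** Under Intervention, "1 live *Lactobacillus* capsule per day will be applied transvaginally for 10 consecutive days starting on the initiation day of the FET cycle". The Abstract has the "capsule vaginally for 10 consecutive days before embryo transfer". The Participant timeline places first use later, once screening and allocation are done: "At the 2nd visit after enrollment, in the control group, participants with LGT dysbiosis will confirm the next contact, while the intervention group will administer" the capsules. Table 3 likewise marks the capsule from the 2nd visit.
- **Time to transfer.** "The duration of endometrial preparation will continue for approximately 14 days" (Participant timeline). The day of embryo transfer (ET) is not fixed.
- **Readout.** In the qPCR section, "The abundance of *Lactobacillus* spp. will be calculated relative to that of total bacteria". Table 1 lists primers for three *Lactobacillus* species and *Gardnerella vaginalis*. The 16S data go to alpha and beta diversity and to a between-group comparison of taxa by LEfSe (Microbiome and metabolism).
- **Product.** A live *Lactobacillus* capsule, identified by approval number, manufacturer and a minimum CFU per gram. Its species is not named.
- **Working line for dysbiosis.** Eligibility requires *Lactobacillus* below 80% of the vaginal microbiome (Inclusion criteria).

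**The concern.** The treatment belongs to the genus that the main microbiome readout measures, and by allocation only one arm receives it. DNA methods count delivered cells, live or dead, together with resident ones. The article describes no viability step, culture, product-strain assay or later swab. Randomization balances the resident flora at baseline, but it cannot separate product from recovery afterwards, because the product is itself the difference between the arms. The Discussion says that control participants can still obtain *Lactobacillus*. That would dilute the contrast without separating its two parts.

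At stake is what the trial can conclude about the first half of its objective and its proposed mechanism. Product that is merely still present on ET day and later cleared would look the same, at genus level, as a restored resident flora. If pregnancy did not improve, the two explanations (flora restored without benefit, or flora never restored) could not be told apart from the genus-level share.

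**Working it through.** The plan states no figure for the gap or the residue, so there is none to reproduce. The sample size concerns clinical pregnancy and does not enter.

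**1. Gap from last capsule to swab.** With start on cycle day *d*, the tenth capsule falls on day *d* + 9, and the gap is ET day − (*d* + 9).

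- Start on day 1 (Intervention) and ET on day 14 (taken from the preparation of about 14 days): 14 − 10 = 4 days.
- Start on day 2, 3, 4 or 5 (possible under the Participant timeline), ET on day 14: 3, 2, 1 or 0 days.
- Assuming ET anywhere from day 12 to day 19, with a day-1 start: 2 to 9 days.

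**2. Effect of residue on the *Lactobacillus* share.** Let *s* be the resident share and *r* the residual product DNA as a multiple of the resident bacterial DNA, with the resident flora unchanged. The measured share is (*s* + *r*)/(1 + *r*). Setting this to 0.80 gives *r* = (0.80 − *s*)/0.20.

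| Resident share *s* | Residue *r* that reads as 80% |
|---|---|
| 79% | 0.05 |
| 60% | 1 |
| 50% | 1.5 |
| 40% | 2 |
| 30% | 2.5 |
| 10% | 3.5 |

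Check at 60%: (0.60 + 1)/(1 + 1) = 0.80. Below the line there is still a shift: from 50%, *r* = 0.25 reads as 0.75/1.25 = 60%, and *r* = 1 reads as 1.50/2 = 75%.

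**3. Effect on other taxa.** A taxon with resident share *x* reads as *x*/(1 + *r*). At *r* = 1 every non-product share halves, including that of *Gardnerella*. For the woman at 60%, the non-*Lactobacillus* share goes from 40% to 0.40/2 = 20% with no organism lost. A lower relative abundance of *Gardnerella*, or a shift in diversity computed over all taxa, is therefore not independent evidence of recovery.

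**4. What added product does not move.** For two non-capsule taxa with resident shares *a* and *b*, the ratio is [*a*/(1 + *r*)]/[*b*/(1 + *r*)] = *a*/*b*. Shares recomputed after the capsule taxon is removed are likewise free of *r*, and so is the absolute load of a non-capsule taxon.

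**5. What cannot be computed.** The documents give CFU per gram as a lower bound only, no capsule weight, no clearance and no resident load. They place no bound on *r* at about 4 days.

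**The case against.** The strongest reply is that ET day is the right time to sample. The trial's rationale is that women with *Lactobacillus* deficiency implant and conceive less often, so the flora at transfer is the relevant exposure. The treatment is called supplementation, so delivered *Lactobacillus* present that day is part of the intended effect. The article does not define reversal as regrowth of resident strains, and its own working line is at genus level. All of this stands. The swab should stay, and its genus-level result is valid as a description of the flora at transfer.

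Other parts also stand. Cervical canal swabs are taken at both times, with care to avoid vaginal contact, from a site that is not dosed directly, although carry-over is possible. 16S gives more than the genus share. The residue is unknown, so the arithmetic shows a possibility and not a likely bias.

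Three stronger readings are tempting but unsupported:

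- *Any rise will be the product.* The documents give no residue, so a rise may equally contain real recovery.
- *Species-level qPCR is limited to baseline.* It is described under quick screening, but the text does not exclude ET-day samples, and swabs from both times go to DNA extraction.
- *The trial will report a false reversal.* No microbiome measure is among the listed primary or secondary outcomes, and how these data become a claim may be set in a plan not shown here.

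What the reply does not remove is the gap between the stated objective and a genus-level share taken within days of dosing. The other readouts, as planned, are relative too.

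**Conclusion.** The point holds as a limit on inference. The only post-treatment swab comes nominally about 4 days after the last capsule: 0 to 4 days across the start days considered with ET on day 14, and 2 to 9 days for a day-1 start if ET falls on day 12 to 19. The planned relative DNA measures mix residual product with resident recovery, so a between-arm rise in *Lactobacillus* share, or a fall in other shares, cannot by itself show that dysbiosis was reversed.

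The size is not known. The residue needed to read as 80% runs from 0.05 of the existing bacterial load for a woman at 79% to 2.5 times that load at 30%. Which of these is realistic cannot be judged from the documents. The result rests on the assumptions that delivered cells contribute DNA at sampling and that ET falls near the end of preparation. Clinical pregnancy, the primary outcome, is not affected.

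**What to change.** 1. **Limit the claim.** Report ET-day genus-level *Lactobacillus* as *Lactobacillus present at transfer*, with days since the last capsule taken from the dated medication diary (Table 2). Do not rest a claim of reversal on it alone.
2. **Name the capsule species** in the protocol.
3. **Add a supporting analysis that added product DNA cannot move**, on the vaginal and cervical samples. Repeat the 16S diversity and LEfSe comparisons after removing the capsule taxon and renormalising, at a common read depth, since product reads use up depth. If sequencing resolves the capsule only to genus, say so, because removal then takes out all *Lactobacillus*. Also compare ratios among non-capsule taxa, for example non-capsule *Lactobacillus* species to *Gardnerella vaginalis*, with the Table 1 primers at both time points and leaving out any target that matches the capsule species. Absolute load in place of share of total bacteria is an alternative. Simply repeating the species qPCR as a share of total bacteria would not do, for the reason in step 3 of the working.
4. **Show both results side by side.** The supporting analysis would miss genuine engraftment of the capsule strain.
5. **Reconcile the capsule start** between Intervention and the Participant timeline with Table 3, since it sets the gap.

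The cost is protocol wording, some analysis, and, if not already planned, species qPCR on the ET-day samples of up to 300 women. No new visit or sample is needed. Absolute quantification, if chosen, would add laboratory work. The restoration figure will probably look less favourable than the genus-level share.

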### DNA extraction and quick screening by quantitative PCR

DNA extraction from a vaginal swab will be performed using the DNeasy Power Soil kit (12888, QIAGEN) according to the manufacturer’s instructions. The quantity and quality of DNA will be assessed by a NanoDrop 2000 (Thermo Fisher Scientific, USA). Quick screening for the relative abundance of *Lactobacillus* spp. in the vaginal microbiome will be performed by qPCR. The relative abundance of *Gardnerella vaginalis* and subtypes of *Lactobacillus* spp., including *Lactobacillus jensenii*, *Lactobacillus crispatus*, and *Lactobacillus ineris,* will also be evaluated. The sequences of primers used in qPCR are presented in Table 1. DNA will be amplified with TB Green® Premix Ex Taq™ (Tli RNaseH Plus) (RR420, Takara) using an ABI QuantStudio™ 7 Flex Real-Time PCR System. The abundance of *Lactobacillus* spp. will be calculated relative to that of total bacteria.

**Table 1 Tab1:** List of primers used for qPCR

Target	Forward	Reverse
Total bacteria	5′-AGAGTTTGATCCTGGCTCAG-3′	5′-GCTGCCTCCCGTAGGAGT-3′
*Lactobacillus* spp.	5′-AGAGTTTGAT/YM/TGGCTCAG-3′	5′-CACCGCTACACATGGAG-3′
*Lactobacillus jensenii*	5′-AAGTCGAGCGAGCTTGCCTATAGA-3′	5′-CTTCTTTCATGCGAAAGTAGC-3′
*Lactobacillus crispatus*	5′-AGCGAGCGGAACTAACAGATTTAC-3′	5′-AGCTGATCATGCGATCTGCTT-3′
*Lactobacillus ineris*	5′-CTCTGCCTTGAAGATCGGAGTGC-3′	5′-ACAGTTGATAGGCATCATCTG-3′
*Gardnerella vaginalis*	5′-TTACTGGTGTATCACTGTAAGG-3′	5′-CCGTCACAGGCTGAACAGT-3′

### Intervention

For the intervention group, a live *Lactobacillus* capsule (> 1 × 10^6^ CFU/g, National Medicine Approval Number: S20030005, Inner Mongolia Shuangqi Pharmaceutical Co., Ltd., PRC) will be administered vaginally.

The live *Lactobacillus* capsule has been reported to be effective for bacterial vaginosis treatment with fewer adverse effects than antibiotics, and probiotic treatment for women with GDM has been reported to improve maternal and infant health outcomes [10, 17–19]. In the intervention group, 1 live *Lactobacillus* capsule per day will be applied transvaginally for 10 consecutive days starting on the initiation day of the FET cycle. Medical gloves will be included in the pill box, and the pills will be stored at 2–8 °C until use. The usage will be explained to the participants by the CRCs. A well-designed medication diary will be prepared to help remind patients and assist them in recording the process of medication administration (Table 2). Regular follow-up will be performed on day 5 and day 10 in both groups by phone call. Any adverse response will be recorded and reported at any time.

**Table 2 Tab2:** Medication diary

Medication diary			
Name:			
Date	Day Month Year	Day Month Year	Day Month Year
Live *Lactobacillus* capsule for vaginal use	□ Morning □ Evening ______pill	□ Morning □ Evening ______pill	□ Morning □ Evening ______pill
	Day Month Year	Day Month Year	Day Month Year
	□ Morning □ Evening ______pill	□ Morning □ Evening ______pill	□ Morning □ Evening ______pill
	Day Month Year	Day Month Year	Day Month Year
	□ Morning □ Evening ______pill	□ Morning □ Evening ______pill	□ Morning □ Evening ______pill
	Day Month Year		
	□ Morning □ Evening ______pill		

Please fill out the date and time after the daily use of 1 capsule

Please contact us if any symptoms of discomfort occur during medication use

### Standard care

All participants in both groups will receive optimally personalized endometrial preparation regimens. The medication regimens will be recorded in detail, including the dose, frequency, and duration of use of the medication.

### Participant timeline

The time schedule of enrollment, intervention, follow-up and outcome assessments is shown in Table 3. After undergoing ovulation, egg retrieval, IVF, and advanced embryo freezing, PCOS patients will move on to the next step of endometrial preparation for FET. The duration of endometrial preparation will continue for approximately 14 days. At the 1st clinical visit on the first day of the current FET cycle, written informed consent, baseline information, 2 vaginal swabs, 2 cervical canal swabs, and 3 ml peripheral blood will be obtained at enrollment. After quick screening for the relative abundance of *Lactobacillus* spp. in vaginal flora, the participants will be informed of whether they have LGT dysbiosis and the results of randomization. At the 2nd visit after enrollment, in the control group, participants with LGT dysbiosis will confirm the next contact, while the intervention group will administer live *Lactobacillus* capsules vaginally and will be provided a medication diary. All participants will be followed up 5 times in the clinic or by phone call. The 3rd visit after 5 days of drug administration will mainly be about whether any adverse response occurs. At the 4th visit after 10 days of drug administration, the medication diary will be checked and reviewed, and any adverse response will be recorded and reported. At the 5th visit on the day of ET, 2 vaginal swabs, 2 cervical canal swabs, and 3 ml peripheral blood will be obtained from participants in both groups. At the 1st follow-up after 14 days of ET, human chorionic gonadotropin (HCG) and progesterone (P) levels will be determined as standard clinical procedures. If the HCG test is positive, the 2nd follow-up will occur approximately 5 weeks after ET, and clinical pregnancy will be confirmed by ultrasound and recorded in the CRIP system. At the 3rd follow-up, the fetal developmental situation and maternal obstetric complications at approximately 24-28 gestational weeks, if any, will be carefully recorded. The endpoint of follow-up is live birth, and maternal and neonatal information will be obtained.

**Table 3 Tab3:** Schedule

	1st visit on FET initial day	2nd visit after enrollment	3rd visit after 5 days	4th visit after 10 days	5th visit on ET	1st follow-up at 14 days after ET	2nd follow-up at 5 weeks after ET	3rd follow-up at mid-pregnancy	End of live birth
**Enrollment**									
Eligibility screen	**X**								
Written informed consent	**X**								
Allocation		**X**							
**Interventions**									
Optimal endometrial preparation	**X**	**X**	**X**	**X**	**X**				
*Lactobacillus* capsule		**X**	**X**	**X**					
**Assessments**									
Baseline questionnaire	**X**								
Vaginal and cervical canal swabs	**X**				**X**				
Peripheral blood samples	**X**				**X**				
Medication diary (intervention group)		**X**	**X**	**X**					
HCG and P						**X**	**X**		
Clinical pregnancy							**X**		
Maternal and Fetal information							**X**	**X**	**X**
Safety assessment		**X**	**X**	**X**	**X**	**X**	**X**	**X**	**X**

*HCG*, human chorionic gonadotropin; *P*, progesterone

### 16S rRNA amplicon sequencing

For the analysis of bacterial diversity, V3-V4 variable regions of 16S rRNA genes will be amplified with universal primer pairs 343F (5′-TACGGRAGGCAGCAG-3′) and 798R (5′-AGGGTATCTAATCCT-3′) [20]. 16S rRNA sequencing will be performed on an Illumina NovaSeq 6000 with 250 bp paired-end reads (Illumina Inc., San Diego, CA; OE Biotech Company; Shanghai, China).

